### Missing data handling

The distribution and potential mechanisms of missing data will be systematically evaluated, with reporting of the proportion of missingness per variable, the missing data pattern (monotone or non-monotone), and comparisons of baseline characteristics between participants with and without missing data. Primary analyses will assume data missing at random (MAR): complete case analysis will be applied when the proportion of missing data is below 5%; when missingness exceeds 5%, multiple imputation by chained equations (MICE) will be performed using 20 imputation datasets, with imputation models incorporating all relevant variables, and results pooled using Rubin’s rules. Sensitivity analyses will employ pattern mixture models (with *δ*-adjustment parameters) and tipping point analyses to evaluate the robustness of study conclusions under alternative missing data assumptions.

### Loss to follow-up

A standardized definition of loss to follow-up will be applied (three consecutive missed follow-up contacts). Data from participants lost to follow-up will be right-censored at the time of their last valid contact. Reasons for loss to follow-up (relocation, withdrawal, death, loss of contact, etc.) will be systematically documented. Baseline demographic and clinical characteristics will be compared between participants lost to follow-up and those who complete follow-up to assess potential selection bias. Inverse probability weighting (IPW) will be applied as needed to statistically correct for informative censoring due to dropout, thereby enhancing the external validity and generalizability of study findings.

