## Methods

### Study design and setting

The Prolonged Disorders of Consciousness Cohort (PDOCC) study is a single-center, prospective cohort study designed to systematically characterize the 5-year natural history and prognostic determinants of VS and MCS. A total of 1,000 eligible participants are planned for enrollment between June 2026 and May 2029, with longitudinal follow-up conducted over 5 years via structured telephone interviews at 3-month intervals. The study will be conducted at the Department of Rehabilitation Medicine, Guangdong Sanjiu Brain Hospital. The enrollment period spans from June 1, 2026 to May 31, 2029 (36 months). The follow-up period is calculated from each participant’s date of enrollment and extends for 60 months, with full cohort follow-up to be completed by May 31, 2034. Data collection encompasses a baseline assessment at enrollment and scheduled follow-up visits at 3, 6, 12, 24, 36, 48, and 60 months. The study protocol has been approved by the Institutional Review Board of Guangdong Sanjiu Brain Hospital (Ethics Approval No. 2026-01-073). Written informed consent will be obtained from all participants or their legally authorized representatives (LARs) prior to enrollment.

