### Follow-up procedures

Follow-up assessments will employ a hybrid surveillance strategy combining in-person evaluations with remote monitoring. Core neurobehavioral and functional assessments (CRS-R, GOS-E, DRS, EQ-5D, SF-36, FIM, HADS, and Zarit Caregiver Burden Interview) will be conducted at bedside by certified assessors at baseline and at 3, 6, 12, 24, 36, 48, and 60 months (8 assessment timepoints in total, comprising 7 in-person follow-up visits). The Chinese validated CRS-R (7) will be used throughout. Assessors must complete standardized training—covering scoring, ≥10 supervised assessments, and ICC ≥ 0.85 reliability—before independent use. The same assessor will evaluate each participant at all timepoints when feasible; if replaced, inter-rater reliability will be verified against the prior assessor’s last two evaluations. Total and subscale scores will be recorded at each visit. eMCS is defined by subscale-specific behavioral thresholds (per Primary Outcome Variables), not a total score of 23/23, which reflects full neurological recovery rather than functional communication or object use. Neuroimaging investigations (MRI/DTI/fMRI) and serum biomarkers (NfL, S100B, GFAP, and other injury-related biomarkers) will be performed at baseline and at 6, 12, 24, 36, 48 and 60 months. Following the 6-month visit, remote follow-ups will be conducted by telephone interview supplemented by caregiver-reported outcomes at 3-month intervals between scheduled in-person visits, primarily capturing vital status, rehospitalization events, and major adverse events. Remote follow-ups will be administered by uniformly trained research coordinators using standardized scripts, with video calls employed as an adjunct to confirm the patient’s general condition. In-person outpatient visits will be conducted by neurologists and rehabilitation therapists.

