Follow-up assessments will capture: changes in consciousness level (CRS-R); vital status; major cardiovascular events; functional independence (Functional Independence Measure [FIM]); health-related quality of life (SF-36); caregiver burden (Zarit Caregiver Burden Interview); changes in medication or treatment regimens; activities of daily living (ADLs) and instrumental activities of daily living (IADLs); mental health status (Hospital Anxiety and Depression Scale [HADS]); and adverse event documentation. All follow-up data will be entered in real time into an electronic data capture (EDC) system, with monthly data quality reviews conducted to achieve a target follow-up completion rate of ≥ 85%.

Outcome event ascertainment procedures are as follows: recovery status will be confirmed through a composite of clinical assessments, medical record review, and neuroimaging evidence (e.g., fMRI or EEG demonstrating improved cortical activity); death events will be ascertained via civil death registration systems, family-reported notification, and hospital records, with cause-specific mortality classified as neurological deterioration, cardiovascular events, infection, or other causes; cardiovascular events will be adjudicated according to internationally accepted definitions supported by neuroimaging and laboratory evidence. Telephone interviews have been established as a feasible follow-up modality, demonstrating agreement with self-reported outcome measures in the majority of settings, achieving a cohort retention rate of 93% within 6 months in culturally adapted intervention research, and proving applicable to the longitudinal assessment of functional and cognitive recovery trajectories following neurological infections (12) (Table 1).

**Table 1 tab1:** Evaluation parameters at baseline and follow-up visits.

Evaluation parameter	Baseline (enrollment)	Follow-up (telephone/video or on-site visits)						
	(Hospital admission)	Visit 1 (3 m)	Visit 2 (6 m)	Visit 3 (12 m)	Visit 4 (24 m)	Visit 5 (36 m)	Visit 6 (48 m)	Visit 7 (60 m)
Informed consent	x							
Inclusion criteria met	x							
Demographics & medical history	x							
Vital signs & neurological exam	x							
Consciousness level (CRS-R)	x	x	x	x	x	x	x	x
Functional status (GOS-E, DRS)	x	x	x	x	x	x	x	x
Quality of life (EQ-5D)	x	x	x	x	x	x	x	x
Survival status	x	x	x	x	x	x	x	x
Rehospitalization & complications	x	x	x	x	x	x	x	x
Adverse events	x	x	x	x	x	x	x	x

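### The loss-to-follow-up rule does not separate telephone calls from CRS-R visits, so it does not fit the recovery endpoint, and it leaves open how a participant who returns is censored

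*Protocol article*

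**What the plan says.** All references are to the protocol article.

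- **Loss rule** (Loss to follow-up): "A standardized definition of loss to follow-up will be applied (three consecutive missed follow-up contacts"). The type of contact is not specified.
- **Censoring** (same section): "Data from participants lost to follow-up will be right-censored at the time of their last valid contact". The section does not define a valid contact and does not mention a participant who comes back.
- **Visits** (Study design and setting): "scheduled follow-up visits at 3, 6, 12, 24, 36, 48, and 60 months". Follow-up procedures counts "8 assessment timepoints in total, comprising 7 in-person follow-up visits" and places the CRS-R there, at the bedside.
- **Calls** (Follow-up procedures): after month 6, "remote follow-ups will be conducted by telephone interview supplemented by caregiver-reported outcomes at 3-month intervals between scheduled in-person visits". The section gives the content of these calls as "primarily capturing vital status, rehospitalization events, and major adverse events".
- **Recovery endpoint** (Primary and secondary outcome variables): it needs at least two CRS-R assessments at least 7 days apart. Survivors who have not met it are censored at month 60.
- **Completion target** (Follow-up procedures, repeated under Bias control): monthly data reviews are meant "to achieve a target follow-up completion rate" of at least 85%. The denominator is not given.
- **Table 1**: the seven follow-up columns are headed "Follow-up (telephone/video or on-site visits"), whereas the Abstract and Follow-up procedures make these visits in-person.

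**The concern.** The two kinds of contact carry different information. A call can show that a patient is alive or has been readmitted. It cannot supply the CRS-R scores that define recovery. A rule that counts both alike can go wrong in both directions for this primary outcome.

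A participant whose CRS-R visits are all attended can be classed as lost because the family was not reached by telephone. A participant with no CRS-R after baseline can stay under observation because the telephone is answered.

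In the first case, observed late recoveries, which the Discussion gives as a reason for the five-year horizon, might be cut off. In the second, unassessed time is counted as time without recovery, which would bias the cumulative incidence of recovery downward if any such patients recover. The completion target has the same weakness: unless its denominator is stated, reaching 85% does not show that recovery was measured.

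**Working it through.** **Step 1. The contact calendar.** Inputs: the visit months from Study design and setting, and the call interval from Follow-up procedures.

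- Visits: months 3, 6, 12, 24, 36, 48, 60. That is 7, which with baseline gives the article's own 8 timepoints.
- Calls between months 6 and 12: month 9, one call.
- Calls in the four annual gaps: 15/18/21, 27/30/33, 39/42/45, 51/54/57, three in each.
- Total calls: 1 + 4 × 3 = 13. Total contacts: 13 + 7 = 20.

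**Step 2. Calls missed, visits attended.** Take a participant seen at month 12 who is not reached at 15, 18 and 21. That makes three missed contacts in a row, so the rule is met at month 21. The last contact was 21 − 12 = 9 months earlier, and the month-24 CRS-R visit is not yet due. The other three annual gaps behave in the same way.

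Suppose the participant then attends months 24, 36, 48 and 60. Two readings are open:

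- Lost status stands once met: censoring at month 12, and 60 − 12 = 48 months and 4 of 7 CRS-R visits are unused. For the later gaps the figures are 36, 24 and 12 months.
- The last valid contact is the last one ever made: that is month 60, and nothing is lost.

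The text does not choose between them.

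**Step 3. Calls answered, visits missed.** The contacts in order are visits at 3 and 6, call at 9, visit at 12, calls at 15/18/21, visit at 24, and so on. With every visit missed and every call answered, the longest run of misses is 2 (months 3 and 6). After that, calls precede and follow every visit up to month 48, so no run exceeds 1. The participant is never lost and, if alive, is censored as unrecovered at month 60 with no CRS-R after baseline.

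**Step 4. How often Step 2 might arise (illustration only).** The article gives no call-miss rate. Assume that each call is missed independently with probability q and that all visits are attended. The chance of at least one annual gap with all three calls missed is 1 − (1 − q³)⁴:

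| q | q³ | 1 − (1 − q³)⁴ |
|---|---|---|
| 0.2 | 0.008 | 3.2% |
| 0.3 | 0.027 | 10.4% |
| 0.4 | 0.064 | 23.2% |

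These are the shares of five-year survivors who would meet the definition at least once. They are not shares of data lost.

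**Step 5. The 85% target.** If the denominator were all 20 contacts, 0.85 × 20 = 17 would suffice. These could be 13 calls and 4 visits, leaving 3 of 7 CRS-R visits (43%) undone. This is one possible denominator. The article does not state any.

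**The case against.** The strongest reply is that the harm comes from a reading the article does not impose. A reader might infer that the participant in Step 2 is irrevocably censored at month 12 and forfeits 48 months and four CRS-R visits. The article nowhere says that lost status is permanent. Taken plainly, a later attended visit becomes the last valid contact. This stands: 48 months is the upper end of a range that starts at zero. A reader might also call this censoring a year back, but when the rule is met the interval is 9 months.

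A reader might likewise infer that the 85% target can be met mainly by telephone. That needs a per-contact denominator. A per-participant rate is at least as natural, since the sample size section anticipates 15% loss, the exact complement. This also stands.

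The article has safeguards too. Bias control plans active tracing of lost participants. Loss to follow-up adds inverse probability weighting as needed and a comparison of lost participants with completers. Missing data handling adds pattern mixture and tipping point analyses. Deaths are also ascertained from civil registration and hospital records. These limit the damage, above all for mortality, but they do not settle the point. Tracing has no stated consequence for a participant who is found. Weighting needs a defined censoring time. In Step 3 no censoring occurs before month 60, so weighting for dropout has nothing to act on.

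Finally, detail on re-entry may sit in a fuller document, and its absence alone would be no finding. But the article does state a definition, and as stated it fits neither its own contact schedule nor an endpoint that depends on CRS-R.

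**Conclusion.** The point holds as a badly fitted rule, not as a demonstrated loss of data. On the article's own schedule, missing only the three calls in one annual gap meets the definition of lost even when CRS-R attendance is complete. Conversely, complete absence of follow-up CRS-R never meets it if the calls are answered. Both follow from the calendar, on the literal reading that a call counts as a follow-up contact.

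The size is not fixed by the documents. In the first case the follow-up lost runs from none to 48 months, depending on how return is treated. In the second, up to 60 months are counted as unrecovered without assessment. The 3.2%, 10.4% and 23.2% rest on assumed independent miss rates of 20%, 30% and 40% and show only who would meet the definition. The Table 1 heading is a separate labelling conflict that adds to the uncertainty about which contacts yield a CRS-R. The change is worth making before enrolment because it concerns a primary outcome and costs little.

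**What to change.** 1. **Loss to follow-up:** define loss and censoring by endpoint. For recovery, base loss on in-person CRS-R visits, state how many must be missed, and censor at the last CRS-R assessment. For mortality, censor at the last known vital status from any source. Add a corresponding line for cardiovascular events.
2. **Same section:** state that a participant who is re-contacted, including through the planned tracing, re-enters follow-up and that all later CRS-R visits count.
3. **Follow-up procedures and Bias control:** state that the 85% target applies to CRS-R visits due among living participants who have not yet met the recovery endpoint. Report call completion separately.
4. **Table 1:** reconcile the follow-up heading with the Abstract and Follow-up procedures, which make the seven visits in-person, and show the telephone contacts in their own columns.

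The cost is wording in these places, with no additional visits or calls. The downside is that the reported completion figure may be lower than one that counts calls.

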### Sensitivity analyses

All sensitivity analyses are prespecified in the study protocol to prevent post-hoc analytical bias. The analytical strategies include: (1) application of alternative outcome definitions (e.g., modified recovery criteria or endpoint adjudication standards); (2) analysis of alternative study populations (per-protocol analysis and as-treated analysis); (3) application of the cause-specific hazard model as an alternative to the Fine-Gray subdistribution hazard model for the primary competing-risk analysis; (4) comparison of results across different missing data handling approaches (complete case analysis, multiple imputation, and single imputation); and (5) evaluation of the impact of alternative covariate adjustment strategies (stepwise adjustment, full model, and reduced model) on effect estimates. Through systematic comparison of results across varying assumptions and analytical methods, the robustness and reliability of study conclusions will be comprehensively assessed.

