#### Exposure variable

The primary exposure variable is the baseline level of consciousness (VS or MCS) at enrollment. All enrolled participants will receive standardized multimodal rehabilitation care in accordance with the Chinese Expert Consensus on the Diagnosis and Treatment of Prolonged Disorders of Consciousness (Standard of Care, SOC) (10), encompassing: (1) pharmacological arousal-promoting therapy (e.g., amantadine, donepezil, zolpidem); (2) multimodal sensory stimulation therapy (auditory, tactile, visual, and olfactory modalities); (3) physical therapy (including tilt-table training and passive mobilization); (4) occupational therapy; (5) speech-language therapy; (6) hyperbaric oxygen therapy (where indicated and available); and (7) neuromodulation techniques (e.g., median nerve electrical stimulation, repetitive transcranial magnetic stimulation, spinal cord stimulation), as well as evidence-based complication management (infections, spasticity, pressure injury). Treatment intensity for each modality will be quantified as total weekly contact time (minutes per week) and session frequency, recorded prospectively in the electronic data capture system at each assessment timepoint. All treatment variables will be incorporated as time-dependent covariates (operationalized as weekly contact time (min/week) per rehabilitation modality) in the analytical models to distinguish the natural disease course from treatment-mediated effects.

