## Discussion

The field of pDoC currently faces two fundamental challenges: first, the absence of large-scale, long-term longitudinal follow-up data in Chinese populations—as existing evidence is predominantly derived from European and North American cohorts (16, 17) and therefore inadequately reflects the disease trajectories shaped by China’s distinct etiological profile, healthcare resource distribution, and rehabilitation culture; second, the predominance of prognostic prediction models based on cross-sectional or short-term follow-up data, which are unable to capture the dynamic evolution of consciousness recovery and consequently deprive clinical decision-making of accurate temporal guidance, resulting in considerable uncertainty in the timing of therapeutic interventions (18). To address these challenges, we designed this single-center, prospective, observational cohort study with a 5-year follow-up period, anchored at the Department of Rehabilitation Medicine, Guangdong Sanjiu Brain Hospital—a nationally recognized leading center for pDoC diagnosis and management. The central objective of this protocol is to establish a high-quality, longitudinal database of long-term outcomes in Chinese patients with pDoC, enabling the systematic characterization of dynamic changes in consciousness recovery, quality of life, and functional status, and the construction of precision prognostic prediction models tailored to the domestic population, thereby providing an evidence base for individualized intervention strategies.

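### The per-protocol and as-treated sensitivity populations do not fit a cohort that assigns no treatment, and would carry selection bias if built from care received after enrolment

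*Protocol article*

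**What the plan says.** The Sensitivity analyses section lists five strategies. The second is "analysis of alternative study populations (per-protocol analysis and as-treated analysis". The same section introduces the list with "All sensitivity analyses are prespecified in the study protocol to prevent post-hoc analytical bias" and ends by judging the robustness and reliability of the conclusions from a comparison of the results.

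The rest of the article describes a study without allocation. The Discussion calls it a "single-center, prospective, observational cohort study with a 5-year follow-up period". Under Exposure variable: "The primary exposure variable is the baseline level of consciousness (VS or MCS) at enrollment". The same section says of care: "All enrolled participants will receive standardized multimodal rehabilitation care in accordance with the Chinese Expert Consensus". Treatment intensity is "recorded prospectively in the electronic data capture system at each assessment timepoint", and "All treatment variables will be incorporated as time-dependent covariates". Under Study design and setting, each participant's follow-up runs for 60 months from the date of enrolment.

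**The concern.** A per-protocol set keeps patients who adhered to what they were assigned. An as-treated analysis regroups patients by what they received instead of what they were assigned. Both need an assignment to depart from. A baseline level of consciousness cannot be adhered to or crossed over from, and the rehabilitation package is meant for every participant, so it defines no groups either.

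Two things are at stake. First, the article presents these analyses as fixed in advance, yet with nothing assigned to anchor them, membership rules would have to be devised later. Second, one obvious rule, grouping by care completed or ever received, makes membership depend on staying alive and unrecovered long enough to qualify. An analysis of that kind could disagree with a sound primary result, or agree with it for the wrong reason, and the article would read either as evidence about robustness.

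**Working it through.** The article states no figure on this point, so there is none to reproduce. The check is a comparison of passages, followed by an illustration on stated assumptions.

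**Step 1: is there an assigned treatment?** No. The design is observational (Discussion), the exposure is VS or MCS at enrolment, and care follows one consensus for all (both under Exposure variable). Neither population has a reference point.

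**Step 2: does the planned handling of treatment cover item (2)?** Time-dependent covariates protect a regression model, because care counts only from when it is received. Item (2) names alternative study populations, that is, sets of patients. A set chosen on later care is already selected before any model is fitted.

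**Step 3: what would selection on completed care do?** The article gives neither a mortality rate nor a care-completion rule. Assumptions: constant independent hazards; recovery r = 0.10 per year in both groups; death d (MCS/VS) = 0.05/0.10, 0.10/0.20 or 0.15/0.30 per year; 30% VS; a patient qualifies by surviving L years; time counted from enrolment.

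The 5-year cumulative incidence of recovery among those who qualify is

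(1 − e^(−rL)) + e^(−rL) × r/(r+d) × (1 − e^(−(r+d)(5−L))).

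Middle scenario:
- L = 0 (everyone). MCS: 0.5 × (1 − e^(−1.0)) = 31.6%. VS: 0.333 × (1 − e^(−1.5)) = 25.9%. Difference 5.7 points.
- L = 1 year. MCS: 0.0952 + 0.9048 × 0.5 × (1 − e^(−0.8)) = 34.4%. VS: 0.0952 + 0.9048 × 0.333 × (1 − e^(−1.2)) = 30.6%. Difference 3.8 points.
- L = 3 and 6 months give differences of 5.2 and 4.7 points.

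All three scenarios, everyone versus L = 1 year:

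| Death hazard MCS/VS | MCS − VS recovery, points | 5-year recovery, both groups | 5-year death, both groups |
|---|---|---|---|
| 0.05/0.10 | 3.6 → 2.3 | 34.1% → 36.1% | 27.3% → 22.4% |
| 0.10/0.20 | 5.7 → 3.8 | 29.9% → 33.4% | 46.5% → 39.1% |
| 0.15/0.30 | 6.9 → 4.8 | 26.5% → 31.1% | 60.2% → 51.8% |

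**Step 4: what would ever-versus-never grouping do?** Simulation of a therapy with no effect: recovery hazard 0.083 per year, death 0.05 to 0.15 per year, half the patients intended for therapy, Cox model from enrolment. The apparent hazard ratio for recovery or death, which should be 1, depends on how late therapy starts:
- starts within 1 month: about 0.95 to 0.99
- within 3 months: about 0.92 to 0.95
- within 1 year: about 0.74 to 0.79
- within 2 years: about 0.59 to 0.63

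**The case against.** A reader might infer that these sets can only be formed from care received after baseline, so that the plan has immortal-time bias built in. The documents do not support that.
- A per-protocol set could rest on eligibility, or on completing baseline data collection within the 2-week window given under Data sources and measurements. Neither needs later care.
- The only handling of treatment that the article states is as time-dependent covariates, repeated in the Discussion. That is the standard guard against immortal time and the opposite of a fixed ever/never grouping. No comparison of treated with untreated patients is planned.
- The large hazard ratios in Step 4 need half the cohort untreated and starts spread over one to two years. The article describes a package for everyone, recruitment from a rehabilitation department and a treatment record at baseline. With early starts the distortion nearly disappears.
- Selection on survival moves absolute incidences. It need not move a cause-specific hazard ratio: with constant hazards, restricting to patients event-free at 3, 6 or 12 months left a true ratio of 1.3 at 1.29 to 1.31.
- Exact analysis-set definitions are commonly left to an analysis plan, and this article is condensed.

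These objections remove the certainty and any fixed magnitude. They do not remove the mismatch. The point is not that a definition is missing, but that the article commits to two populations its design cannot give their usual meaning. A per-protocol set based on baseline compliance would be nearly harmless, but the text does not say that is meant, and it would not rescue the as-treated analysis, which by its name groups on treatment received.

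**Conclusion.** The point holds as a mismatch between a stated analysis and the design: with no assigned treatment, per-protocol and as-treated populations are not a meaningful robustness check. Bias is conditional. It arises if the sets are built from care received or completed after enrolment with time zero at enrolment, and it does not arise from that source if they use baseline criteria only. Its size cannot be fixed from the documents, and every figure in Steps 3 and 4 rests on assumed hazards and membership rules. The matter is confined to one of five sensitivity strategies; the primary analysis, endpoints and sample size are unaffected.

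**What to change.** In item (2) of Sensitivity analyses, delete the per-protocol and as-treated analyses. Replace them with populations defined only by data known at enrolment, for example patients enrolled within a stated time of injury, or patients without pre-existing neurological disease. Both items are already to be recorded.

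If treatment received is of interest, keep it as the time-dependent covariate already planned. Alternatively, use a landmark at the scheduled month-3 visit: include patients alive and unrecovered then, classify them by treatment up to that visit, and count only later events.

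The cost is a change to one list item and about the same analysis work. The landmark version loses all events before month 3, and its results apply only to patients who reach that visit without an event.
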